# Treatment of carpal tunnel syndrome with wrist splinting: study protocol for a randomized placebo-controlled trial

**DOI:** 10.1186/s13063-019-3635-6

**Published:** 2019-08-27

**Keywords:** Carpal tunnel syndrome, CTS, Median nerve, Wrist, Non-surgical treatment, Splinting, Randomized trial, RCT

## Abstract

**Background:**

Carpal tunnel syndrome (CTS) is a common cause of pain, weakness, sensory loss, and activity limitations. Currently, the most common initial treatment is use of a rigid splint immobilizing the wrist, usually during night-time, for several weeks. Evidence regarding the efficacy and effect durability of wrist splinting is weak. The treatment is associated with costs and may cause discomfort and limit daily and work activities. No placebo-controlled trials have been performed.

**Methods:**

This is a randomized controlled trial designed to assess the efficacy of a rigid wrist splint compared with soft wrist bandage (placebo) in patients with primary idiopathic CTS. The trial will be conducted at an orthopedic department. Patients, 25 to 65 years old, who seek primary health-care with symptoms of CTS will be screened, and potentially eligible patients will be referred to the study center. Patients who fulfill the trial’s eligibility criteria will be invited to participate. A total of 112 patients who provide informed consent will be randomly assigned to treatment with either a rigid wrist splint or a soft bandage to be used initially for 6 weeks at night and, if possible, during the day. The splints and bandages will be fitted with a temperature-monitoring device to measure the total time during which they have actually been worn. The trial participants will complete a questionnaire that includes the 6-item CTS symptoms scale (CTS-6); the 11-item disabilities of the arm, shoulder, and hand (*Quick*DASH) scale; and the EuroQol 5-dimension (EQ-5D) health status and quality-of-life measure at baseline and at 6, 12, 24, and 52 weeks after treatment start. The participants will undergo physical examination and nerve conduction testing at baseline and at 52 weeks. The trial’s primary outcomes are the change in the CTS-6 score from baseline to 12 weeks and the rate of carpal tunnel release surgery at 52 weeks.

**Discussion:**

This is the first placebo-controlled randomized trial with electronic monitoring of actual splint use and will provide evidence regarding the efficacy of wrist splinting in patients with CTS.

**Trial registration:**

ISRCTN Registry, ISRCTN81836603. Registered on May 5, 2018.

**Electronic supplementary material:**

The online version of this article (10.1186/s13063-019-3635-6) contains supplementary material, which is available to authorized users.

## Background

Carpal tunnel syndrome (CTS) is a very common cause of hand pain, weakness, and loss of sensation leading to limitations in daily activities, work disability, and worsening quality of life [1]. The prevalences in the adult general population are about 5% among women and 2% among men [2]. The goal of treating CTS is to relieve symptoms and improve hand function. Currently, the most common non-surgical treatment across the world is splinting the wrist with a rigid splint, usually at night, sometimes combined with other treatments [3]. There is some evidence that wrist splinting may be effective in the short term [4–6], but the evidence is generally weak, the optimal duration of treatment is unclear, and the long-term efficacy has not been established [7, 8]. Treatment benefit of wrist splinting itself has often been small and of short duration, but in trials that compared splinting with surgery [5, 9], the benefit has often been augmented by large cross-over to surgery [10]. The rationale behind wrist splinting is that it prevents wrist flexion, known to increase pressure in the carpal tunnel [11]. However, the duration of splinting currently used in clinical practice (4 to 6 weeks) is not based on clear evidence [7]. The long-term effect of splinting the wrist for this short time on the pathophysiological factors involved in the causation of CTS may not be large. It is unclear why the benefit from wrist splinting in idiopathic CTS can persist after cessation of splinting.

In previous randomized studies, treatment of CTS with wrist splint has been compared with surgery [5] or other non-surgical treatments, such as steroid injection or exercises [7, 12]. Of the non-surgical treatments, only local steroid injection has strong evidence from placebo-controlled trials supporting short-term efficacy [12]. However, it is still an invasive procedure not routinely available in primary care and thus may require referral to specialists. The few randomized studies that evaluated wrist splinting in the treatment of patients with CTS were not placebo-controlled and therefore the reported improvement may have been related to non-specific effects or the natural course of the disease. Compliance in wearing the splint was often not evaluated or was assessed by asking patients to register data in a diary, a method with uncertain reliability. A previous study has shown that patients tend to overestimate their splint use [13].

Although splinting is a simple and safe treatment, it has some disadvantages. Patients may find that wearing a splint is uncomfortable and limits them in some work or daily activities or both. The costs of the splint and therapy visits may be high [14]. There is a need for a randomized placebo-controlled trial assessing the efficacy of wrist splinting in the treatment of patients with CTS.

### Trial objective

The objective of the trial is to evaluate the placebo-controlled treatment efficacy and effect durability of wrist splinting in patients with primary idiopathic CTS up to 12 months after treatment start. Our hypothesis is that, in patients with CTS, wearing a rigid wrist splint at night and, if possible, during the day for 6 weeks is more effective than wearing a soft wrist bandage in reducing symptoms and subsequent need for surgery.

## Methods

### Trial design and setting

The study is a prospective randomized parallel-group superiority clinical trial conducted at one university health-care orthopedic department (Department of Orthopedics, Hässleholm-Kristianstad-Ystad) in collaboration with several primary care centers in the region of Northeastern Skåne in southern Sweden (population of 300,000). The department is the only referral facility for patients with CTS in that region. The Standard Protocol Items: Recommendations for Interventional Trials (SPIRIT) checklist is provided as an Additional file 1.

### Inclusion criteria

Primary, idiopathic CTSAge 25–65 years, either sexSymptoms of classic or probable CTS according to the criteria in the Katz hand diagram [15]Two surgeons (specialists in orthopedic or hand surgery) independently diagnose the patient’s CTSSymptom duration of at least 1 month

### Exclusion criteria

CTS classified as severe (thenar muscle atrophy or 2-point discrimination exceeding 8 mm in at least one finger)Treatment of the study hand with a wrist splint in the past 12 monthsPrevious steroid injection for CTS in the study handInflammatory joint diseaseVibration-induced neuropathyPolyneuropathyCurrent pregnancyTrauma to the study hand in the past 12 monthsPrevious CTS surgery in the study handInability to complete questionnaires because of language difficulties or cognitive disorderSevere medical illnessKnown abuse of drugs or alcohol or both

### Screening

Patients consulting a primary care physician or referred to occupational therapists at primary health-care centers for symptoms suggestive of CTS will be screened. Potentially eligible patients are referred to the orthopedic department and scheduled for assessment by two surgeons in the research team (a senior hand surgeon and an orthopedic specialist) within 1 to 2 weeks of referral. Both surgeons will be present when a full history is taken, but the following physical examination will be carried out by the orthopedic specialist only. Patients judged to fulfill the eligibility criteria are then given, by the orthopedic specialist, full verbal and written information about the aims and conduct of the trial as well as the potential advantages and disadvantages of participation. Patients who accept participation will provide written informed consent. Participants will undergo the baseline assessment immediately and nerve conduction testing as soon as possible but no later than 2 weeks after enrolment. Only one hand will be included in the trial (in bilateral symptoms, the hand with the worse score on the 6-item CTS symptoms scale (CTS-6) will be included). Each patient will be allowed to enter the trial only once.

### Randomization

Patients will be randomly assigned in accordance with a computer-generated randomization list (ratio of 1:1) [16]. The randomization will be stratified in accordance with patient sex and carried out in random blocks of various sizes (4, 6, and 8). An administrative assistant, not involved in the trial, will prepare sequentially numbered sealed opaque envelopes containing the group allocation. After providing written informed consent and undergoing the baseline assessment by a study investigator (orthopedic surgeon), the enrolled patient will proceed to the hand therapist, who will open the envelope with the lowest number and provide the patient with either a wrist splint with a metal bar or a soft bandage in accordance with treatment allocation (Fig. 1).

**Fig. 1 Fig1:**
[figure not shown]
Patient flow through the trial

### Interventions

#### Group A: Splint with metal bar

The patients will receive a standard splint (model Base, Catell AB, Hägersten, Sweden) with wrist in neutral position to be worn at night and, if possible, during the day (Fig. 2). No other instructions or treatments will be given. If after 6 weeks the patient reports large improvement, no further treatment will be given. If the patient reports small or no improvement, further treatment with the same splint will be given for 4 weeks. If the patient reports small or no improvement after 10-week splinting, the patient will be offered surgery. Patients who refuse further treatment with wrist splinting will be offered surgery. Surgery will not be performed before 12 weeks after treatment start.

**Fig. 2 Fig2:**
[figure not shown]
Conventional splint containing a metal bar and a temperature-monitoring device (**a**), holding the wrist in neutral position (**b**)

If symptoms recur after improvement, the patients will be treated with 4 weeks of wrist splinting using the same type of splint. If after 4 weeks the patient reports small or no improvement, the patient will be offered surgery. Patients who refuse further treatment with wrist splinting will be offered surgery.

#### Group B: Soft bandage

The patients will receive a custom-made (neoprene) wrist bandage to be worn at night and, if possible, during the day (Fig. 3). No other instructions or treatments will be given. If after 6 weeks the patient reports large improvement, no further treatment will be given. If the patient reports small or no improvement, the patient will be offered surgery. Surgery will not be performed before 12 weeks after treatment start.

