#### Surgery

The decision to choose to have surgery will be made by the patient, on the basis of the experienced severity of current symptoms and activity limitations, in consultation with an orthopedic surgeon not involved in the trial and blinded to the patient’s group allocation. Surgery will be performed by specialists in orthopedics or hand surgery not involved in the trial, in accordance with usual practice at the department.

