#### Secondary endpoints

Change in the 6-item CTS symptoms score from baseline to 6 weeks and 52 weeksChange in *Quick*DASH score from baseline to 12 weeks and 52 weeksChange in patient satisfaction score at 12 weeks and 52 weeksChange in EQ-5D index from baseline to 12 weeks and 52 weeksCost-effectiveness at 52 weeksPalmar pain score at 52 weeksTime to surgery within 52 weeksDuration of sick leave during 52 weeksChange in grip strength from baseline to 52 weeksAdverse events at 52 weeks

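### Week-6 non-responders follow different rules in the two arms, so both primary endpoints compare two treatment pathways and not the 6-week splint effect hypothesised

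*Protocol article*

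**What the plan says.** All references are to the Protocol article.

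- **Hypothesis** (Trial objective): wearing a rigid splint at night and, where possible, "during the day for 6 weeks is more effective than wearing a soft wrist bandage" in reducing symptoms and the later need for surgery.
- **Group A, little or no improvement at week 6** (Interventions, Group A): "If the patient reports small or no improvement, further treatment with the same splint will be given for 4 weeks". Then: "If the patient reports small or no improvement after 10-week splinting, the patient will be offered surgery". Patients who refuse more splinting are offered surgery, so the extension is optional.
- **Group B, same report at week 6** (Interventions, Group B): "If the patient reports small or no improvement, the patient will be offered surgery". No further bandage course and no week-10 reassessment are set out.
- **What is the same in both arms:** the wear instruction for the first 6 weeks, the 4-week rule for recurrence after improvement, and the bar on surgery before week 12.
- **Primary endpoints, in rank order:** CTS-6 change from baseline to 12 weeks, then rate of surgery at 52 weeks. Testing is by intention to treat. The surgery endpoint can support a confirmatory claim only if the CTS-6 null hypothesis is rejected first (Statistical analysis).
- **Abstract, Methods:** the devices are "to be used initially for 6 weeks at night and, if possible, during the day". This wording covers both devices, but only Group A has a week-6 extension.

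**The concern.** The protocol matches the arms on everything around the device except the rule for week-6 non-responders. Both primary endpoints are measured after that rule has acted.

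**12-week CTS-6.** Some Group A patients will have been prescribed a splint until week 10. CTS-6 asks about the past two weeks, so their 12-week score describes the time just after an active course. A Group B non-responder has no prescribed course after week 6. Duration matters in this trial because the Background says that "the optimal duration of treatment is unclear" and questions the evidence for the usual 4 to 6 weeks. A claim that 6 weeks of splinting works could in fact rest on a longer course.

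**52-week surgery rate.** A Group A non-responder must fail twice, or refuse more splinting, before surgery is offered. A Group B non-responder must fail once. The surgery rates therefore reflect two offer rules as well as two devices.

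**Working it through.** **1. The plan's own figure.** Sample size inputs: difference 0.7 − 0.1 = 0.6, SD 0.9, two-sided 5%, power 90%. n = 2 × (1.960 + 1.282)² × 0.9² / 0.6² = 47.3, so 48 per group as stated. Recruiting 112 gives 56 per arm. The t-test has 89.8% power at 48 per arm and 93.8% at 56. The sample size is not in dispute.

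**2. Planned exposure before the 12-week score.** Let p be the share of non-responders at week 6 and a the share of these who accept the extension. The document gives neither, so both are assumed. Mean Group A exposure = 6 + 4pa weeks.

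| p | a | Group A mean (weeks) | Excess over 6 weeks |
|---|---|---|---|
| 0.2 | 0.5 | 6.4 | 7% |
| 0.6 | 0.5 | 7.2 | 20% |
| 0.6 | 1.0 | 8.4 | 40% |
| 0.8 | 1.0 | 9.2 | 53% |

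The comparator of 6 weeks for Group B is itself uncertain. The section on discontinuing or modifying interventions asks participants in general to continue where possible. It ends by asking the participant to stay on the allocated treatment until surgery, which cannot happen before week 12. Suppose this applied to everyone awaiting surgery and 70% of those offered it accept. Group B would then average 6 + 6 × 0.6 × 0.7 = 8.5 weeks up to week 12. Group A (p = 0.6, a = 1) would average 8.4 weeks, or 8.4 + 2 × 0.6 × 0.7 × 0.7 = 9.0 weeks if the 70% of non-responders still unimproved at week 10 did the same. The gap could therefore be about half a week and not 2.4 weeks.

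**3. Surgery rate when the arms differ only in the offer rule.** Assumed inputs: p = 0.6 in both arms, uptake u = 0.7, and r = share of non-responders who improve between weeks 6 and 10. Let d be the share of Group B late improvers who decline the surgery already offered. Let s be the share of Group A late improvers' expected operations that still happen after relapse, since the recurrence rule leads to a surgery offer.

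Group A rate = pu(1 − r + rs). Group B rate = pu(1 − rd). RR = (1 − r + rs) / (1 − rd), which equals 1 exactly when d + s = 1.

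The rejection rates are by exact binomial enumeration, 56 per arm, two-sided 5%, for the pooled chi-squared test and an unadjusted log-RR Wald test.

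| r | d | s | A | B | RR | Chi-squared | Log-RR |
|---|---|---|---|---|---|---|---|
| 0.3 | 0 | 0 | 0.294 | 0.420 | 0.70 | 28.7% | 26.5% |
| 0.3 | 0 | 0.2 | 0.319 | 0.420 | 0.76 | 19.6% | 18.0% |
| 0.3 | 0.5 | 0 | 0.294 | 0.357 | 0.82 | 11.2% | 10.0% |
| 0.3 | 0.5 | 0.2 | 0.319 | 0.357 | 0.89 | 7.2% | 6.3% |
| 0.3 | 1 | 0 | 0.294 | 0.294 | 1.00 | 5.1% | 4.4% |
| 0.3 | 0.8 | 0.2 | 0.319 | 0.319 | 1.00 | 5.2% | 4.5% |
| 0.3 | 1 | 0.2 | 0.319 | 0.294 | 1.09 | 6.1% | 5.4% |
| 0.1 | 0 | 0 | 0.378 | 0.420 | 0.90 | 7.1% | 6.6% |

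**4. Effect of the ranked testing.** The rates above ignore the ranking. If the splint has no effect on CTS-6, a surgery claim through the ranking is wrong at most about 5% of the time. If the planned CTS-6 effect holds, the first test is passed about 93.8% of the time, and a log-RR rejection rate R becomes something between R − 6.2 points and R: 20.3% to 26.5% in the top row, 3.8% to 10.0% for d = 0.5 and s = 0.

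**The case against.** **The CTS-6 issue is one of labelling.** The bandage serves as placebo. If rigid splinting does nothing specific, 4 more weeks of it add nothing specific. A reader might infer that a positive 12-week result would say nothing about the splint. The document does not support that: the result would still show an effect of rigid splinting, and only the dose is misdescribed. The first sentence of the objective speaks of wrist splinting up to 12 months with no 6-week limit, and the extension is stated openly. All of this stands. But the hypothesis itself names 6 weeks.

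**The exposure gap may be small.** The text on continuing until surgery can be read as covering Group B patients who wait for an operation, and 6 weeks of bandage is not a strict stop for non-responders. The sentence follows a passage on severe symptoms or declining treatment, so its scope is arguable. On either reading Group B gets no prescribed extension and no second assessment.

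**The surgery bias may be nil.** A reader might infer that the surgery comparison is loaded in favour of the splint. The document does not establish this. Patients decide "on the basis of the experienced severity of current symptoms and activity limitations", with a surgeon outside the trial who is blinded to allocation, and the week-12 bar leaves Group B time to improve and decline. Group A improvers can relapse and be offered surgery. The RR of 0.70 needs no Group B improver to decline and no Group A improver to relapse, which is an extreme case. The 20% to 26% range under the ranking also needs a 0.6-point symptom benefit that leaves surgery demand unchanged, which is strained when demand follows symptoms.

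**A reason for the asymmetry may exist** in the full protocol. A reason would explain the design but would not make the endpoints match a 6-week hypothesis.

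**Conclusion.** The concern holds as a mismatch between hypothesis and design, and it should be fixed. It rests on the text alone: two rules for the same week-6 report, a 6-week hypothesis, and both primary endpoints measured later.

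- **12-week CTS-6:** a positive result would support 6 weeks of splint with an optional 4-week extension. Planned Group A exposure is up to 10 weeks. The arm average is 6.4 to 9.2 weeks for the assumed 20% to 80% non-response and 50% to 100% acceptance. How far this exceeds Group B depends on how the instruction to continue until surgery is applied.
- **52-week surgery rate:** the unequal offer rules can bias the comparison, but neither size nor direction follows from the document. With 30% assumed late improvement the RR from the rule alone runs from 0.70, through 1.00 when d + s = 1, to slightly above 1 when d + s exceeds 1 (1.09 in the case shown).

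Confidence is high for the mismatch. A material bias in the surgery rate is possible and not shown.

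**What to change.** Restate the hypothesis, and the confirmatory claims on both primary endpoints, as a comparison of two pathways: 6 weeks of splint with an optional 4-week extension and a surgery offer after week 10, against 6 weeks of bandage with a surgery offer after week 6. Name one endpoint that is already secondary, "Change in the 6-item CTS symptoms score from baseline to 6 weeks", as the key supportive test of the device at equal planned exposure.

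This changes the wording of the objective and the analysis plan only. It needs no new data, visits or patients, and the sample size stays as it is. The claim becomes narrower, and the 6-week contrast does not test whether benefit lasts after the device is stopped. Rewording also leaves the unequal offer rules in place, so the surgery result must be reported as a difference between pathways.

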**Fig. 3 Fig3:**
[figure not shown]
Soft bandage (**a**) allowing full wrist flexion (**b**) and extension (**c**)

If symptoms recur after improvement, the patient will use the same type of bandage for 4 weeks. If after 4 weeks the patient reports small or no improvement, the patient will be offered surgery. Patients who refuse further treatment with the wrist bandage will be offered surgery.

#### Discontinuing/modifying allocated interventions

The trial interventions (wrist splint or soft bandage) are not expected to cause harms, but it is possible that a participant will experience discomfort using a splint or bandage. Participants will be asked to continue their allocated intervention if possible. The participants are informed that, in case of worsening of symptoms during intervention, they contact the trial therapist, who will discuss the case with the investigators. If the worsening is not experienced by the participant as severe, the participant will be asked to continue the allocated intervention in accordance with the protocol. If symptoms are severe or the participant declines to continue the allocated treatment, surgery will be offered. The participant will be asked to continue the allocated treatment until surgery.

#### Concomitant care

No other treatments will be prescribed during the trial interventions. The information provided to participants will not specify any prohibitions. Participants will be able to take non-prescription analgesics. Cross-over between the trial interventions is not allowed.

### Follow-up procedures

Patients will complete a questionnaire consisting of disease-specific and generic patient-reported outcome measures at baseline and at 6, 12, 24, and 52 weeks after treatment start and will attend physical examination and nerve conduction testing at 52 weeks (Fig. 4). The trial coordinator (experienced research nurse) will monitor completeness of questionnaires and use telephone contact when necessary. Participants who choose to undergo surgery will be asked to complete the questionnaire shortly before surgery if the date of surgery precedes or is more than 2 weeks after the scheduled follow-up dates. Participants will be informed, in writing and during examination/follow-up, about the importance of completing the intervention and the follow-up procedures. Patients who choose to discontinue intervention are asked to, if possible, respond to the outcome questionnaires at the intervals defined in the protocol and attend the 1-year follow-up.

